### **Comparative Period**

- Interview and physical examination.
- Hematology (as above).
- Blood biochemistry (as above).
- Pain and QOL scores (CTCAE v5.0 / v3.0, PRO-CTCAE #3a, 3b, EORTC QLQ-OH15 #35, pain NRS).
- Presence, site, and timing of oral mucositis.
- Presence and timing of oral candidiasis.
- Intraoral photographs.
- Confirmation of concomitant medications/therapies.

- Evaluation of procedural factors.
- Patient preference or acceptability of the investigational treatment.
- ECOG PS.
- Patient diary entries (once daily) including:
  - Device dislodgement (presence/absence),
  - Pain intensity (PRO-CTCAE #3a, #3b; EORTC QLQ-OH15 #35; pain NRS),
  - Number of as-needed anti-inflammatory analgesic tablets,
  - Number of uses of oral steroid ointment as rescue medication,
  - Use of *Episil*® oral liquid (yes/no).
- Adverse events.
- Device malfunctions.
- G-CSF administration (yes/no).

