### 3. Quality of Life (QOL) Assessment [Patient-Reported Outcomes]

- PRO-CTCAE v1.0 (Items #3a and #3b)
- EORTC QLQ-OH15 (Item #35)
- Pain NRS at affected site

The *Pain NRS* will be derived from the patient diary and represents the maximum pain level during each treatment period.

The scale ranges from **0 to 10**:

- 0: no pain
- 1–3: mild pain
- 4–6: moderate pain
- 7–10: severe pain (10 = “unbearable pain, worst ever experienced”)

4. **Occurrence site and timing of oral mucositis**

Evaluated across all intraoral regions (upper/lower labial vestibule, tongue dorsum/right/left/ventral/tip, buccal mucosa, palate, others), and specifically at the designated affected site.

5. **Subgroup analyses** by chemotherapy regimen for preventive and pain-relieving efficacy.

6. **Chemotherapy completion status** (treatment adherence).

7. **Number of as-needed anti-inflammatory analgesic tablets** (from patient diary).

8. **Number of rescue uses of oral steroid ointment** (from patient diary).

9. **Use of Episil® oral liquid** (presence/absence; patient diary).

10. **Technical performance assessment**

Evaluation of natural, brushing-related, eating-related, and self-induced device dislodgement.

11. **Patient preference for continued use of the investigational treatment**

Evaluation of participants' willingness to continue using the device.

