## **3) Analysis of Secondary Endpoints**

### **Secondary Endpoints:**

1. Same as the primary endpoint during the continuous period.
2. Oral mucositis and oral pain grades (CTCAE v5.0 / MedDRA/J v25.1).
3. QOL: PRO-CTCAE v1.0 (#3a, #3b), EORTC QLQ-OH15 (#35), Pain NRS at the affected site.
4. Site and timing of oral mucositis onset.
5. Subgroup analysis by chemotherapy regimen for prevention/improvement outcomes.
6. Chemotherapy completion status.
7. Use of concomitant as-needed anti-inflammatory analgesics (from patient diary).
8. Frequency of oral steroid ointment as rescue medication (patient diary).

9. Use of Episil® oral liquid (patient diary).
10. Technical performance assessment.
11. Patient preference for continuation of the investigational device.

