#### **Statistical Methods:**

- For items (1)–(2), analyses identical to those for the primary endpoint will be applied.
- For item (5), subgroup analyses by chemotherapy regimen will be performed similarly.
- For other items:
  - Categorical data: same as primary analysis (frequencies, percentages, chi-square).
  - Continuous data: summary statistics (as above), estimation of intergroup differences and 95% CIs, and use of two-sample Wilcoxon or two-sample t-tests depending on distribution.
  - Analyses will also be performed on *change from Day 1*.
  - *Pain NRS* will be analyzed both as a continuous variable and as categorical (0 = none, 1–3 = mild, 4–6 = moderate, 7–10 = severe).
  - For participants with multiple affected sites, the worst score per period will be used.

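### The four ordered Pain NRS bands are tested with a chi-square that ignores their order, and the protocol has no rule for other ordered secondary items

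*Protocol*

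**What the plan says.** Protocol section 8(2), under Statistical Methods for the secondary endpoints, sorts the items without a rule of their own into two branches. The first is "Categorical data: same as primary analysis (frequencies, percentages, chi-square"). The second, for continuous data, gives summary statistics, a between-group difference with 95% CI, and "use of two-sample Wilcoxon or two-sample t-tests depending on distribution". There is no third branch for ordered categories.

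Pain NRS is placed in both branches: it "will be analyzed both as a continuous variable and as categorical (0 = none, 1–3 = mild, 4–6 = moderate, 7–10 = severe").

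The other patient-reported items appear in section 6(2), item 3, as "PRO-CTCAE v1.0 (Items #3a and #3b") and QLQ-OH15 item #35, and again in section 8 as "QOL: PRO-CTCAE v1.0 (#3a, #3b), EORTC QLQ-OH15 (#35), Pain NRS at the affected site". Neither place says whether they are categorical or continuous. Section 5(2), Comparative Period, lists them as "Pain and QOL scores (CTCAE v5.0 / v3.0, PRO-CTCAE #3a, 3b, EORTC QLQ-OH15 #35, pain NRS"). Section 8 adds "Analyses will also be performed on" change from Day 1.

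**The concern.** In the primary analysis the chi-square compares a yes/no outcome (prevention or improvement achieved), for which it is well suited. On a two-arm table with four ordered columns it answers a different question. It spends 3 degrees of freedom on asking whether the distributions differ in any way, and it does not use the fact that severe is worse than mild. The question for these items is directional: does the device shift patients towards less pain?

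Two consequences follow. A moderate, consistent shift towards milder pain is more likely to be missed than with a test that uses the order. And a significant result does not by itself show that pain was reduced.

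The matter deserves attention because the trial's title and objective include pain relief, while the primary CTCAE v3.0 criteria in section 6(1) grade erythema, ulceration, necrosis and bleeding. Evidence on pain therefore comes from secondary items, the site-specific NRS among them.

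**Working it through.** **The plan's own figure.** Section 7 gives 50% v 25%, two-sided 5%, 90% power, Pearson chi-square. With mean proportion 0.375:

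n = [1.960·√(2·0.375·0.625) + 1.282·√(0.5·0.5 + 0.25·0.75)]² / 0.25² = (1.342 + 0.848)² / 0.0625 ≈ 76.7, so 77 per arm.

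Power at 77 is 90.1%. The stated size reproduces. The protocol gives no power target for any secondary item.

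**Inputs for the comparison.** From the protocol: 77 per arm, 1:1 allocation, two-sided 5%, four NRS bands. Assumed, because the protocol does not give them: the control distributions, five levels as an illustration for the other items, and a proportional-odds shift.

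**Building the alternative.** Multiply the cumulative odds in the control arm by OR. For control 40/30/20/10% and OR 2, the cumulative proportions 0.40, 0.70, 0.90 have odds 0.667, 2.333, 9. Doubled, these are 1.333, 4.667, 18, giving 0.571, 0.824, 0.947. The intervention distribution is therefore 57.1/25.2/12.4/5.3%.

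**Simulated power**, 40,000 trials per cell: Pearson chi-square on the full table v tie-corrected Wilcoxon, in %.

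| Control distribution (%) | OR 1.5 | OR 2 | OR 3 |
|---|---|---|---|
| 25/25/25/25 | 19.0 v 28.8 | 49.3 v 66.2 | 89.4 v 96.2 |
| 40/30/20/10 | 17.5 v 27.3 | 44.9 v 62.8 | 85.0 v 94.2 |
| 25/35/25/15 | 18.5 v 28.6 | 47.8 v 65.5 | 88.0 v 95.7 |
| 60/25/10/5 | 14.5 v 23.3 | 35.9 v 53.1 | 72.1 v 86.7 |
| 80/12/6/2 | 9.0 v 15.3 | 19.1 v 33.1 | 41.2 v 61.3 |
| 20/20/20/20/20 | 17.1 v 29.3 | 44.8 v 67.2 | 86.9 v 96.6 |
| 40/25/20/10/5 | 15.2 v 27.2 | 40.2 v 63.3 | 81.4 v 94.5 |
| 60/20/10/7/3 | 12.3 v 23.0 | 30.9 v 53.0 | 66.7 v 86.7 |

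Over OR 1.5 to 3 (OR 2.5 was also run) the gap is 6.4 to 20.1 points for four levels and 9.7 to 23.6 for five. The 23.6 is at OR 2.5 with control 60/20/10/7/3 (50.8 v 74.4).

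**Outside that range.** At OR 1.25 the gap is 2.8 to 4.3 points. At OR 5 it is 0.2 to 5.7 points in seven of the eight distributions, and 17.2 points for 80/12/6/2, where power is still well below 100%.

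**Analytic check.** If both tests carry the same noncentrality λ, power is P(χ²(df, λ) > critical value). For 80% power on 1 df, λ = (1.960 + 0.842)² ≈ 7.85. The same λ gives 64.5% on 3 df (loss 15.5 points) and 59.5% on 4 df (loss 20.5 points), in line with the simulation.

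**Where the ranking reverses.** When the ratio of intervention to control proportions does not move steadily along the scale, the chi-square wins:
- 25/25/25/25 v 15/40/35/10: 81% against 9% for Wilcoxon.
- 40/30/15/15 v 40/30/28/2: 83% against 7%.

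The second pattern is a pure move from severe to moderate, so the rank test's insensitivity is not confined to patterns without benefit.

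**The case against.** Much of the case on the other side stands.

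- **The NRS is already tested with its order in use.** A reader might infer that a real shift in NRS pain would be missed. The documents do not support that: the scale "will be analyzed both as a continuous variable and as categorical", and the continuous branch uses Wilcoxon or a t-test with a difference and CI. Only the banded comparison is affected, and a rank test on the bands partly repeats the continuous analysis on a coarser scale.
- **PRO-CTCAE and QLQ-OH15 are not assigned to chi-square.** A reader might infer that they are. They are called scores, and change from Day 1 is to be analysed, which fits the numeric branch at least as well. Assigning each item to a branch could be left to the SAP. For these items the gap is the missing rule, not a fixed wrong test.
- **The multi-column table is itself a reading.** Referring back to the primary analysis could mean a responder proportion. But section 8 defines prevention and improvement only for the CTCAE outcomes and none for the NRS bands, so a comparison across four bands is the natural reading.
- **Pain does not rest on these items alone.** CTCAE v5.0 oral pain is a separate secondary endpoint with its own directional definition.
- **The chi-square is valid.** The argument concerns efficiency and interpretation, and the planned frequencies show the direction of any difference.

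What remains is that bands with a stated order are sent to the only categorical test named, and that test discards the order.

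**Conclusion.** The point holds in a limited form. For the banded Pain NRS, the protocol names a test that ignores order. For PRO-CTCAE #3a/#3b and QLQ-OH15 #35 it leaves open whether the same test applies. Under a proportional-odds shift of OR 1.5 to 3 with 77 per arm, the cost is roughly 6–20 points of power for four levels and 10–24 for five.

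Those figures are conditional on the assumed distributions, the assumed five levels and proportional odds, and should not be quoted as a property of this trial. It is tempting to anchor them on OR 3, the odds ratio of 50% v 25%, that is (0.5/0.5)/(0.25/0.75). But that planning value belongs to the binary mucositis outcome and says nothing about the size of a shift in pain items.

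The primary comparison and the sample size are not touched. This is a worthwhile improvement to a secondary analysis, not an error that invalidates it.

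**What to change.** In section 8(2), Statistical Methods for secondary endpoints, limit the chi-square to binary and unordered items and add a rule along these lines:

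*Ordered categorical items (Pain NRS bands, PRO-CTCAE #3a and #3b, EORTC QLQ-OH15 #35) are compared between groups by the Wilcoxon rank-sum test with mid-ranks. Frequencies and percentages per level are reported as description.*

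A proportional-odds model with the Day 1 level as covariate is a sound alternative. One of the two should be named in advance, since the trial is open-label. Naming the items also settles which rule PRO-CTCAE and QLQ-OH15 follow. If the SAP already does this, the protocol sentence need only be aligned with it.

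The cost is one or two sentences. No new data, visits or participants are needed, and the Wilcoxon test is already named in the same section. The downside is less sensitivity to non-monotone differences, including a change confined to the severe band. The tabulated frequencies per level keep such a change visible.

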**Rationale for Endpoint Selection:**

- Items 1–3 (excluding localized NRS): internationally standardized measures for QOL in oral mucositis.
- *Localized NRS*: captures pain limited to the specific mucosal site.
- Item 4: assesses overall oral mucositis occurrence.
- Items 5–9: necessary to evaluate efficacy of the investigational device.
- Item 10: required for assessing technical feasibility of device application.
- Item 11: necessary for evaluating patient acceptability and continued use.

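### Onset timing (secondary endpoint 4), if analysed under the generic continuous-data rule, would be compared only among participants who developed mucositis, so that comparison cannot see prevention and may show a spurious shift in onset

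*Protocol*

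**What the plan says.** Protocol Section 6(2) lists item 4 as "Occurrence site and timing of oral mucositis", "Evaluated across all intraoral regions" and also at the designated affected site. The endpoint rationale says that the item "assesses overall oral mucositis occurrence". Section 8(2) 3) repeats it as "Site and timing of oral mucositis onset". Section 5(2) has "Presence, site, and timing of oral mucositis" collected in the comparative period.

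The statistical methods in Section 8(2) 3) state: "For items (1)–(2), analyses identical to those for the primary endpoint will be applied". Item 5 (regimen subgroups) is handled similarly. All remaining items, including item 4, follow a rule by data type:

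- "Categorical data: same as primary analysis (frequencies, percentages, chi-square");
- for continuous data, summary statistics, between-group differences with 95% CIs, and "use of two-sample Wilcoxon or two-sample t-tests depending on distribution".

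The protocol does not say which branch onset timing takes. It contains no time-to-event method, no censoring rule and no value for a participant without onset.

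**The concern.** A participant in whom mucositis is prevented has no onset day. In Section 8(2) 2) that participant counts as a success, but in a t-test or Wilcoxon test on onset days the same participant is simply absent. The null hypothesis becomes: among those who developed mucositis, onset day has the same distribution in both arms. Developing mucositis is a post-randomisation outcome that the device is meant to change, so the two subsets are no longer the randomised groups. This remains so even if every onset date is recorded perfectly.

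Two consequences follow for this comparison. If the device prevents lesions evenly over the cycle, the remaining onset days look alike and the test finds nothing. If it prevents lesions mainly at one stage of the cycle, the remaining onset days differ merely because of which lesions are left, and the result could be misread as the device hastening or delaying onset. The rule also calls for analysis of change from Day 1, which has no meaning for an onset day. That suggests the rule was not written with this endpoint in mind.

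**Working it through.** **The plan's own figure.** The protocol states no figure for item 4. Its sample size (Section 7: 50% v 25%, two-sided 5%, 90% power, Pearson chi-square) reproduces:

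n = [1.960·√(2·0.375·0.625) + 1.282·√(0.50·0.50 + 0.25·0.75)]² / 0.25² = (1.342 + 0.848)² / 0.0625 ≈ 76.7, so 77 per arm. Power at 77 is 90.1%.

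**Inputs for the timing comparison**

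- 77 per arm, 1:1 (Sections 7 and 4(7)).
- Standard comparative period of 21 days (Section 4(3)).
- Control onset 40%, the background figure for chemotherapy patients in Section 3. Device onset 20% is an assumption.
- As an upper bound, 75% v 50%: the complement of the success rates in Section 7. It is an upper bound because failures there also include unimproved baseline mucositis.
- All participants free of mucositis on Day 1 (assumption).
- Control onset days uniform over Days 3 to 21 (assumption), except in the proportional-hazards scenario, where onset times are exponential.

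**Who remains in the test at 40% v 20%.** Control 77 × 0.40 ≈ 31; device 77 × 0.20 ≈ 15. So 154 − 31 − 15 = 108 participants have no onset day.

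**Direction of a spurious shift.** The control mean onset is (3 + 21)/2 = Day 12. If the device removes only onsets after the midpoint, Days 3 to 12 remain, with mean 7.5, a difference of −4.5 days. If it removes only the earlier onsets, Days 13 to 21 remain, with mean 17, a difference of +5.0 days. In neither case was any individual lesion moved.

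**Simulation (2,000 trials per scenario).** Wilcoxon is on onset days among affected participants. Log-rank is on all participants, with event-free participants censored at the end of the period; its column gives the share of trials significant in favour of the device.

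| Onset, control v device | How prevention acts | Mean difference in onset day, device minus control | Wilcoxon significant | Log-rank favours device |
|---|---|---|---|---|
| 40% v 20% | unrelated to timing | 0.0 | 4.4% | 78% |
| 40% v 20% | proportional hazards | +0.5 | 5.4% | 79% |
| 40% v about 20% | only late onsets prevented | −4.5 | 78%, all towards earlier onset | 63% |
| 40% v about 20% | only early onsets prevented | +5.0 | 86%, all towards later onset | 89% |
| 75% v 50% | unrelated to timing | 0.0 | 4.9% | 88% |
| 75% v 50% | proportional hazards | +1.1 | 14% | 92% |
| 75% v 50% | late onsets preferentially prevented | −2.3 | 52%, all towards earlier onset | 68% |
| 75% v 50% | early onsets preferentially prevented | +2.4 | 56%, all towards later onset | 97% |

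The t-test behaves alike (4.6% in the first row). A separate simulation with other onset shapes at 40% v 20% agrees: with constant hazard, Wilcoxon 6% and log-rank 79%; with a wave of onsets around Day 8 (SD 3), 5% and 78%. With only 60 or 46 per arm free of mucositis on Day 1, Wilcoxon stays at about 4 to 6% and log-rank falls to 58 to 67%.

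**What the other analyses still see.** Chi-square on occurrence, 40% v 20%, 77 per arm: z = [0.20·√77 − 1.960·√(2·0.30·0.70)] / √(0.40·0.60 + 0.20·0.80) = (1.755 − 1.270)/0.632 ≈ 0.77, a power of about 78%.

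**The case against.** Four objections carry weight.

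- **The continuous reading is inferred.** The protocol never places timing in the continuous branch. Section 6(2) schedules item 4 at screening, Day 1 and the end-of-period or discontinuation visits, and its rationale speaks of occurrence. If timing were tabulated in categories with no onset as one of them, the stated chi-square would see prevention. This stands as a limit. Even so, a between-group difference with a t-test or Wilcoxon test is what the rule prescribes for an onset day.
- **A Wilcoxon test need not exclude anyone.** Ranking event-free participants after every observed onset gives about 77% power at 40% v 20%. The exclusion is strict only for the t-test. But the protocol states no such convention, and its between-group difference in days would still have no value for these participants.
- **Prevention is tested elsewhere.** A reader might infer from 5% against 78% that the trial loses some 73 points of power and would miss a preventive effect. The documents do not support that. The two tests ask different questions, and the primary endpoint, CTCAE v5.0 prevention and a chi-square on occurrence (about 78% power) all count event-free participants.
- **Reversal depends on assumption.** A reader might infer that the plan will report a preventive device as harmful. That requires late lesions to be preferentially prevented, and Section 3 lists causes of mucositis without saying when each acts. Preventing early lesions gives the opposite shift.

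An unseen analysis plan could add a ranking or censoring convention. The point here, however, is a method that the protocol states and that fits this variable badly, not a detail it leaves open.

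**Conclusion.** The point holds for the timing part of secondary endpoint 4, on the natural reading that onset day is continuous. As written, the comparison conditions on having developed mucositis. At an assumed 40% v 20% onset it rejects in about 5% of trials when prevention is unrelated to timing. When prevention depends on timing, it can show a shift of several days in either direction, including apparently earlier onset with the device.

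The sizes rest on the assumed 20% device rate, the general 40% background rate, the assumed onset distributions and freedom from mucositis on Day 1. The loss of a randomised comparison depends on none of these figures, only on event-free participants being left out.

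Nothing here affects the primary analysis, the sample size of 77 per arm or the trial's ability to detect prevention through its other endpoints. It is worth correcting because a p-value and CI from this comparison could be misread in the report, and the correction is cheap.

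**What to change.** In Protocol Section 8(2) 3), and in the analysis plan, take onset timing out of the generic continuous-data rule:

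- Among participants free of mucositis on Day 1, analyse time from Day 1 to first onset in the comparative period. Censor event-free participants at their end-of-period or discontinuation assessment.
- Present Kaplan-Meier cumulative incidence by arm and a log-rank test stratified by study site, the randomisation stratum in Section 4(7). Censoring also deals with periods of 14, 21 or 28 days.
- State how the onset date is established. The daily diary items in Section 5(2) do not include mucositis onset, and the end-of-period visit has a window of −7 to +7 days. If onset is known only between visits, use an interval-censored equivalent.
- Report onset day among affected participants descriptively only, without a p-value or between-group CI.

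The cost is a short change of text, with no additional patients and no added assessments. The small downside is that the result is a cumulative-incidence or hazard comparison rather than a difference in mean onset day.

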### **4. Method of Randomization**

Before the start of the study, the Randomization Supervisor will prepare a reproducible randomization table using computer-generated random numbers.

A stratified block randomization method will be applied, stratified by study site planned to conduct the comparative period.

The allocation ratio between the intervention and control groups will be **1:1**, based on the planned total sample size.

As this is an open-label study, detailed algorithmic parameters of the randomization will not be described in this protocol to prevent predictability of assignment and potential selection bias. Instead, they are specified in a separate *Randomization Specification Document*, which will remain confidential until all participants have been assigned.

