**Timing of Assessments:**

- Items 1–5: Screening / registration, Day 1 of the comparative period, end (or discontinuation) of comparative period, and end of continuous period.
- Items 6–11: End (or discontinuation) of comparative period, and end of continuous period.

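### Pain NRS, and any other secondary score treated as continuous, is compared unadjusted both as a raw value and as change from Day 1; one model adjusted for the Day 1 score would be at least as precise and give one lead answer

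*Protocol*

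**What the plan says.** Section 8(2) 3), Statistical Methods, covers the secondary endpoints. Continuous data get summary statistics, a between-group difference with 95% CI, and "use of two-sample Wilcoxon or two-sample t-tests depending on distribution". The same list then states "Analyses will also be performed on" change from Day 1. No covariate appears and no analysis is named as the lead. For pain NRS the section adds that it "will be analyzed both as a continuous variable and as categorical", with four bands.

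Three other places bear on this:

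- Section 6(2), Timing of Assessments, schedules "Items 1–5: Screening / registration, Day 1 of the comparative period" among the time points. Item 3 holds PRO-CTCAE #3a and #3b, QLQ-OH15 #35 and pain NRS, so their Day 1 scores exist.
- Section 6(2), item 3, says that the pain NRS comes from the diary and "represents the maximum pain level during each treatment period".
- Section 4(7) 4 describes block randomisation "stratified by study site planned to conduct the comparative period". Section 3 gives four institutions.

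**The concern.** The raw comparison ignores the Day 1 score. The change comparison subtracts it in full, which amounts to fixing its regression slope at 1. A model that estimates the slope from the data uses the same information better and returns one estimate.

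Two things are at stake. One is precision on patient-reported scores that the trial collects anyway. The other is clarity: two tests of one score can fall on opposite sides of 5%, and the protocol does not say which one is to be read. For pain NRS the categorical analysis is a third result. The trial is open-label, which is one more reason to settle the lead result beforehand.

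**Working it through.** **The plan's own figure.** Section 7 gives 77 per arm for 50% versus 25%, two-sided 5%, 90% power, Pearson chi-square. The uncorrected two-proportion formula returns 77 per arm (power 90.1%). This figure belongs to the binary primary endpoint and is not affected. The protocol gives no SD, correlation or power for the continuous scores.

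**Variances.** Let r be the correlation between Day 1 and follow-up scores and k the ratio of the Day 1 SD to the follow-up SD. Both are assumptions. In units of the follow-up variance:

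- raw value: 1
- change from Day 1: 1 + k² − 2kr
- baseline-adjusted: 1 − r²

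Raw minus adjusted is r². Change minus adjusted is (1 + k² − 2kr) − (1 − r²) = (k − r)². Neither can be negative, so the adjusted analysis is never less precise in large samples. It ties with raw at r = 0 and with change at k = r. Change is worse than raw only when 1 + k² − 2kr > 1, that is, when r < k/2.

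**Power.** Take a difference for which the raw test has 80% power with 77 per arm. That is 2.80 × √(2/77) = 0.45 SD. Power for relative variance v is then Φ(2.80/√v − 1.96).

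| r | k | Variance: change | Variance: adjusted | Power: raw | Power: change | Power: adjusted | Adjusted minus change |
|---|---|---|---|---|---|---|---|
| 0.2 | 0.5 | 1.05 | 0.96 | 80% | 78.1% | 81.6% | 3.5 points |
| 0.2 | 1 | 1.60 | 0.96 | 80% | 60.1% | 81.6% | 21.5 points |
| 0.3 | 0.5 | 0.95 | 0.91 | 80% | 82.0% | 83.6% | 1.6 points |
| 0.3 | 1 | 1.40 | 0.91 | 80% | 65.8% | 83.6% | 17.8 points |
| 0.5 | 0.5 | 0.75 | 0.75 | 80% | 89.9% | 89.9% | 0 |
| 0.5 | 1 | 1.00 | 0.75 | 80% | 80% | 89.9% | 9.9 points |
| 0.7 | 1 | 0.60 | 0.51 | 80% | 95.1% | 97.5% | 2.4 points |

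At r = 0.3 and k = 0.5 the change score beats the raw value, as the condition r < k/2 predicts (0.3 > 0.25).

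**Which part of the range is plausible.** Section 10(1) does not require mucositis at entry, so many Day 1 scores may be at or near zero. The follow-up pain NRS is a maximum over the period. Both facts suggest a low r, and both also make equal SDs (k = 1) hard to assume.

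**Agreement of the two planned tests.** Simulation with normal data, k = 1, 77 per arm, 8,000 runs for each of r = 0.2, 0.3, 0.5 and 0.7:

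- At the 0.45 SD effect, the raw and change t-tests disagree on significance in about 20% to 29% of trials.
- With no effect, at least one is significant in about 9% of trials, against about 5% for the adjusted model.

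**The case against.** The strongest reply is that nothing here is invalid. Randomisation protects both planned tests, the endpoints are secondary, and the protocol ties no success claim to them. The word "also" before the change analysis can be read as making it supplementary. Covariate adjustment of secondary endpoints is often left to the SAP, which is not at hand. Most of this stands and sets the priority. It does not remove the point, because the protocol does not leave the method open: it names two unadjusted tests and no lead.

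Four stronger readings are tempting, and the documents do not support them:

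- **A large loss of power.** The 18 to 22 points over the change score need k = 1. At k = 0.5 the gain is about 2 to 4 points. Against the raw test it is also only about 2 to 4 points at r = 0.2 to 0.3.
- **Change always loses to raw when r is below 0.5.** That too holds only for k = 1. In general the condition is r < k/2.
- **The pain claim in the title rests on these scores alone.** Secondary endpoint 2 includes the CTCAE v5.0 oral pain grade, which has its own baseline-referenced definitions of prevention and improvement and is analysed like the primary. Analgesic tablet counts also bear on pain.
- **Every patient-reported item is tested twice by t or Wilcoxon.** Only pain NRS is expressly called continuous. PRO-CTCAE #3a and #3b and QLQ-OH15 #35 are single items, and the protocol does not say whether the continuous or the categorical rule applies to them.

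It is also fair to say that swapping in a model chosen after seeing the distribution would leave the answer just as open. The fix has to settle that choice beforehand.

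**Conclusion.** The point holds as an efficiency and clarity matter, firmly for pain NRS and conditionally for the other item 3 scores. That adjustment is never less precise needs no assumption about r or k beyond large-sample theory. The size of the gain does. From a raw-test power of 80% it is about 2 to 4 points at r = 0.2 to 0.3 and 10 points at r = 0.5. Over the change score at r = 0.2 to 0.3 it runs from about 2 to 4 points (k = 0.5) to 18 to 22 points (k = 1). The disagreement and either-test rates rest on normal data with equal SDs.

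A reader might infer bias, or a weakness in the primary analysis or sample size. Neither follows. This is an optional improvement of low priority.

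**What to change.** In Section 8(2) 3), name one lead analysis for pain NRS and for any other score that is to be treated as continuous, and say which scores those are. The lead analysis would be an ANCOVA of the comparative-period score on arm, Day 1 score and site, reporting the adjusted difference and its 95% CI.

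Decide in advance, and not from the observed distribution, whether ANCOVA or a rank-based or ordinal version with the same covariates is used. If many zeros are expected, the latter may suit better, but a proportional-odds model reports an odds ratio and not a mean difference, so the estimate must be defined to match. Keep the raw and change-from-Day-1 results as descriptive summaries.

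The cost is wording, plus about four extra model parameters (three for four sites, one for the Day 1 score) at N = 154. No new data are needed.
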